## Abstract

**Background:**

Transition from pediatric to adult diabetes care is a high risk period during which there is an increased rate of disengagement from care. Suboptimal transition has been associated with higher risks for acute and chronic diabetes-related complications. The period of emerging adulthood challenges current systems of healthcare delivery as many young adults with type 1 diabetes (T1D) default from diabetes care and are at risk for diabetes complications which are undetected and therefore untreated. Despite the importance of minimizing loss to follow-up there are no randomized control trials evaluating models of transition from pediatric to adult diabetes care.

**Methods/Design:**

This is a multicentre randomized controlled trial. A minimum of 188 subjects with T1D aged between 17 and 20 years will be evaluated. Eligible subjects will be recruited from three pediatric care centres and randomly assigned in a 1:1 ratio to a structured transition program that will span 18 months or to receive standard diabetes care. The structured transition program is a multidisciplinary, complex intervention aiming to provide additional support in the transition period. A Transition Coordinator will provide transition support and will provide the link between pediatric and adult diabetes care. The Transition Coordinator is central to the intervention to facilitate ongoing contact with the medical system as well as education and clinical support where appropriate. Subjects will be seen in the pediatric care setting for 6 months and will then be transferred to the adult care setting where they will be seen for one year. There will then be a one-year follow-up period for outcome assessment. The primary outcome is the proportion of subjects who fail to attend at least one outpatient adult diabetes specialist visit during the second year after transition to adult diabetes care. Secondary outcome measures include A1C frequency measurement and levels, diabetes related emergency room visits and hospital admissions, frequency of complication screening, and subject perception and satisfaction with care.

**Discussion:**

This trial will determine if the support of a Transition Coordinator improves health outcomes for this at-risk population of young adults.

**Trial registration:**

Trial Registration Number: NCT01351857

## Background

Transition from pediatric to adult medical care of adolescents and young adults with T1D has been a challenging issue for decades. A recent American Diabetes Association (ADA) Position Statement [1] highlighted that transition from pediatric to adult diabetes care is a high risk period during which there is an increased rate of disengagement from care. Suboptimal transition has been associated with higher risks for acute and chronic diabetes-related complications. Yet, the question of how best to transition young T1D patients remains unanswered, in part due to lack of randomized control trials evaluating models of transition from pediatric to adult diabetes care.

### Factors associated with suboptimal glycemic control

Many challenges are faced during adolescence by young adults who are establishing personal identity, sexual behaviors and increasing independence. It is a period of transition regardless of their health status due to the increasing influence of peers combined with other contributing societal factors. For anyone coping with the daily demands of managing a chronic disease, young adulthood is even more complex. Diabetes control may deteriorate significantly during this period due to multiple factors including: physiological insulin resistance associated with hormonal changes of puberty, psychosocial distress, risk taking behavior, intentional insulin omission for weight loss or attention, and eating disorders [2,3]. Adolescence is therefore a particularly vulnerable period in diabetes care. In addition, one of the major changes that occur in a young person’s life during this time is the transition from pediatric to adult medical care. Emerging adults may have limited experience with basic tasks often routinely managed by parents, such as scheduling their own medical appointments and maintaining prescribed medical supplies [4]. The transition from pediatric to adult care also may coincide with a loss of health insurance coverage and an increase in financial barriers to healthcare access [5].

### Impact on glycemic control and diabetes related complications

Transition of care has a major impact on blood glucose control and disease outcomes in patients with T1D [6-8]. In the first year of transition 11- 41% of T1D patients drop out of adult medical care [9-11] and 46% report difficulties with the transition process [9]. In a retrospective study, 27% of patients were not followed in an Adult Diabetes Service three years after the last pediatric visit [12].

Individuals who are lost to follow-up have higher A1C values during the 2 years prior to transition of care [13]. This suggests that this poorly controlled population is especially vulnerable to disengagement. Risk factors for poor compliance after transfer to adult diabetes care include female gender, no college degree, poor glycemic control and fewer diabetes care visits in the year prior to transfer [14,15]. The following barriers to successful transition have been identified by individuals with T1D: abrupt transfer of care, lack of accessibility of adult-care services, lack of coordination between different disciplines involved in the care and lengthy waiting periods [14,16].

The impact of loss to follow-up on the health of transitioning youth is significant. Among those lost to medical follow-up, the mean A1C is on average 1.5% higher than those who maintain medical follow-up [13,17-20]. Background retinopathy increases from 5% to 29% [17] and nephropathy by 17% [21]. A 38% pregnancy loss was reported in a group that had no intervention during transition, compared to none in a group who used a central, coordinated navigation service for care, education, and support [22]. Furthermore, diabetes related hospitalization rates increase significantly from 7.6 to 9.5 cases per 100 patient-years in the two years after transition to adult care [21]. UK data for the 20–29 age group show that mortality is increased three fold in men and six fold in women when compared with the general population [15]. The major causes for mortality are acute complications, with 68% of diabetes–related deaths being due to diabetic ketoacidosis (DKA) or hypoglycemia [15].

### Transition interventions

Transition support programs improve the quality of diabetes care in young adults with T1D. A study on the impact of a transition education program at a Toronto diabetes centre reported that the implementation of this program was associated with a decrease in the proportion of patients lost to follow-up from 24% to 7% [10,23]. Studies assessing the role of a transition coordinator have found 0.13% lower A1C levels per visit for the first 4 visits when a transition coordinator was consistently involved with the care of young adult T1D patients [24]. Other studies have demonstrated that a structured transition which includes a collaborative effort between adult and pediatric endocrinology results in a 23% decrease in rates of loss to follow-up for up to three years after transition [12]. There was also a significant reduction in admission rates with DKA to approximately 2/3 of the admission rates prior to the program [24]. The number of eye and feet examinations, and microalbuminuria testing were significantly higher in the structured transition group [12,21]. A recent systematic review on effectiveness of various transitional programs identified patient education programs and joint pediatric/adult clinics or specific young adult clinics as services that may improve outcomes in emerging adults with T1D. However, as the authors suggested, the comparative benefit of different components of these complex interventions is not yet clear. It is noted that successful programs also include a transition coordinator role [25]. Finally, structured transition programs have been found to be feasible and acceptable by young T1D adults [9].

### Transition trial

#### **
*Aim of the study*
**

The overall goal of the study is to determine if a structured transition program for adolescents and young adults with T1D improves diabetes clinic attendance and management as well as glycemic control after transition from pediatric to adult diabetes care.

#### **
*Study objectives*
**

The primary objective of the study is to test the hypothesis that the proportion of young adult T1D patients who fail to attend regular diabetes care during the first year after completion of a structured diabetes transition program will decrease when compared to the proportion of non-attendance of those patients receiving standard care. The secondary objectives of the study are to compare the frequency of routine diabetes testing (A1C, microalbuminuria, lipid profile, and retinal exam) as well as rates of hospitalizations for diabetes related problems (DKA and hypoglycemia), and patient satisfaction with the transition process between the groups.

## Methods/Design

### Design

A multicentre, randomized, single-blind controlled trial is being conducted in two tertiary centres (St Joseph’s Health Care and Children’s Hospital, London Health Sciences Centre in London; Children’s Hospital of Eastern Ontario and The Ottawa Hospital in Ottawa) and a secondary centre (Trillium Health Partners, in Mississauga, Ontario). A minimum of 188 subjects are being randomly assigned in a 1:1 ratio to a structured transition program that spans 18 months or to receive standard diabetes care. The structured transition program is a multidisciplinary, complex intervention designed to provide additional support in the transition period. Central to the program is a Transition Coordinator who provides transition support and is the link between pediatric and adult diabetes care. In addition, the Transition Coordinator offers transitional education and clinical support where appropriate. Subjects are seen in the pediatric care setting for 6 months and then transferred to the adult care setting where they are seen for one year. There will then be a one-year follow-up period for outcome assessment. This study has been approved by each clinical site’s local institutional review board (London REB 17892, Ottawa REB 12/11E and 20120169-01H and Mississauga REB 518). Informed consent is obtained from all study participants based on a template provided by the study group (each approved by the local ethics review board) and centrally monitored by the JDRF Canadian Clinical Trial Network (JDRF CCTN).

### Participants

Subjects with T1D who are between ages 17 and 20 years are recruited from the tertiary and secondary specialized pediatric diabetes clinics in the three participating centres in London, Mississauga, and Ottawa. Only residents of Ontario are eligible since the outcomes are to be determined using the large administrative database available only for residents of this province. All diabetes patients scheduled for a visit with the pediatric diabetes team who are approaching transition age (range 17 to 20) are eligible. However, readiness for transition is not assessed formally as part of this study and is at the discretion of the investigators to determine the most appropriate age for transition according to standard current clinical practice. Factors considered are: future career plans, social situation, and geographic relocation. For example an approximate time for transition coincides with completion of high school which in Ontario ranges from age 17 to 19 years. Subjects are included only if able to independently manage their diabetes and those with an intellectual disability requiring caregiver assistance with diabetes management are not eligible for the study. Subjects with ongoing medical issues that interfere with diabetes care and glycemic control, such as high dose steroid treatment or active cancer treatment, are not eligible either. To allow for adjustment to the diagnosis and minimize the impact of residual insulin secretion on glycemic control, subjects are included only if diagnosed with T1D for at least a year.

### Inclusion criteria

1. Established T1D diagnosis for a minimum of one year.

2. Between the ages of 17 and 20 years.

3. At least 1 visit during the previous year with the pediatric endocrinologist at one of the three participating Diabetes Clinics (aim is to minimize non-adherence with the intervention).

4. Ability to participate in all aspects of this clinical trial.

5. Written informed consent/assent must be obtained and documented.

6. Resident of Ontario.

### Exclusion criteria

1. Pregnant or lactating females or intent to become pregnant during the next 3 years.

2. Condition(s) which in the opinion of the investigator may interfere with the subject’s ability to participate in the study.

3. Prior enrolment in the current study.

4. Prior enrolment of a sibling in the current study.

5. Current participation in another clinical trial or participation in another clinical trial in the 6 months prior to enrolment.

### Sample size and statistical analysis

The outcome measure used to calculate sample size is the proportion of subjects who fail to attend diabetes clinic visits during the second year after transfer to adult care. A 60% relative reduction in non-attendance rate is considered clinically important. The drop out rate, defined as non attendance at adult diabetes clinic during the previous year, for young adults transferred from pediatric to adult diabetes care within the London sites between January 2005 and December 2008 was determined to be 28%, consistent with the literature (unpublished observation). Assuming the non-attendance rate in the control group to be 28% (to detect an absolute difference of 16% (i.e., 28% non-attendance rate in the control group compared to 12% in the intervention group), a total of 188 subjects (94 per group) are required to provide 80% power at the 0.05 level of significance. The sample size calculation did not account for loss to follow-up as this is the primary outcome. The primary analysis will be based on comparison of subjects in the two treatment groups who attend 0, 1, and 2 sessions during the one year follow- up period after completion of the intervention. The Cochran-Mantel-Haenszel mean score test will be used. A 2-sided probability of type 1 error of 0.05 will be declared statistically significant. To control for covariates of interest, the proportional odds model will be adopted. Multilevel growth curve modeling will be used to analyze the glycemic control measurements. Multiple linear regression and logistic regression will be applied to control for covariates of interest where applicable. Reporting of the trial will follow the CONSORT guidelines [26,27].

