a. Questionnaires (Diabetes Quality of Life Measure; Client Satisfaction Questionnaire; Diabetes Distress Scale)

2. Physical examination measures

a. Anthropometric measurements: height, weight, and BMI

a. Blood Pressure

a. Systems physical examination: general survey, skin, head, neck, chest, heart, abdomen, musculoskeletal/extremities, and neurologic (including lower extremity monofilament testing)

3. Laboratory measures

a. A1C (centralized)

a. Fasting lipid profile

a. Urine pregnancy test (females)

#### **
*Randomization*
**

Eligible subjects who have signed informed consent are randomly assigned in a 1:1 ratio to either a structured transition program or to receive standard diabetes care. The randomization schedule is computer generated in variable blocks stratified by 1) centre and 2) the visit 1 A1C (< 8.5% or ≥ 8.5%). The Research Assistant informs the participant of the Randomization group assigned. If the participant is randomized to the Intervention Group, the Research Assistant notifies the Transition Coordinator. Figure 1. provides a flow chart of participants through the study.

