**Figure 1 F1:**
[figure not shown]
**Transition flow diagram.** *Losses to follow up are considered the primary outcome.

#### **
*Blinding*
**

Due to the nature of the intervention it is not possible to blind participants and members of the interdisciplinary team to group allocation. However, data analysis personnel and outcome assessors are blinded to the group assignment. To minimize the possible bias, the allocation sequence is concealed until the subject qualifies for the study and the intervention is assigned. A potential source of bias is treatment cross contamination which is minimized by not permitting any contact between the Transition Coordinator and the control group for the duration of the study, having the consent process conducted by the Research Assistant for both groups, and aiming for physicians to provide the same standard of care to both groups by not being involved in the delivery of the intervention or discussions of the implications. The Canadian Diabetes Association 2008 clinical practice guidelines for the management of T1D patients will be followed in both groups [28].

#### **
*Transition intervention*
**

Subjects randomized to the intervention group are enrolled in the transition program.

The structured transition program is a multidisciplinary, complex intervention aiming to provide additional support during the transition period. The intervention lasts 18 months, 6 months in pediatric care and 12 months in adult care. Table 1 illustrates the study timeline.

**Table 1 T1:** Transition study timeline

**Type of care**	**Pediatric**			**Adult**			**Follow-up**	
	**Visit 1**	**Visit 2**	**Visit 3**	**Visit 4**	**Visit 5**	**Visit 6**	**Visit 7**	**Visit 8**
**Month**	0	3	6	10	14	18	23	28
**Control**	Pediatric Team	Pediatric Team*	Pediatric Team	Adult Endo, DEC	Adult Endo	Adult Endo	Adult Endo	Adult Endo
**Intervention**	Pediatric Team	Pediatric Team*	Pediatric Team	Adult Endo, DEC	Adult Endo	Adult Endo	Adult Endo	Adult Endo
	+ TC	+ TC	+ TC	+ TC	+ TC	+TC		

TC – Transition Coordinator, DEC – Diabetes Education Centre, Endo – Endocrinology clinic.

^*^Referral to Adult Endocrinology Clinic and Diabetes Education Centre takes place.

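### Equating loss to follow-up with the primary outcome fails for subjects whose attendance the Ontario database cannot see, so it does not justify a sample size with no allowance

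*Protocol article*

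**What the plan says.** In the protocol article, under Sample size and statistical analysis, the planning rates are "28% non-attendance rate in the control group compared to 12% in the intervention group", and "a total of 188 subjects (94 per group) are required to provide 80% power at the 0.05 level of significance". The same section adds: "The sample size calculation did not account for loss to follow-up as this is the primary outcome". The footnote to Figure 1 reads: "Losses to follow up are considered the primary outcome". Neither statement separates reasons for loss.

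The Primary outcome section is narrower. The event is having no adult specialist visit in the second year after transition.

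On the data source, the Participants section says that "the outcomes are to be determined using the large administrative database available only for residents of this province". Ontario residence is an inclusion criterion. The Summary of study measures makes use of the health-service records depend on the participant's consent. The Recruitment section sets a goal of 200, which is 12 above the minimum of 188.

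**The concern.** Loss from observation and failure to attend care are different events, and in this design they separate in both directions.

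- A subject who stops all study contact but stays in Ontario with linkage consent in force is still classifiable from the database. That subject is not lost for the primary outcome.
- A subject who leaves Ontario or withdraws linkage consent may see a specialist regularly and yet show no visit in the data. Read literally, the two statements make that subject a primary-outcome event.

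The reason given for making no allowance covers disengagement only. Two things are at stake. If unobservable subjects are coded as failures at the same rate in both arms, the treatment difference shrinks and power falls. If the rates differ, the estimate is biased. Unequal rates are possible because participants are not blinded and only one arm has contact with the Transition Coordinator.

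**Working it through.** **Inputs from the protocol article.** Non-attendance 28% (control) and 12% (intervention); 94 per group; 80% power; 1:1 allocation; "A 2-sided probability of type 1 error of 0.05 will be declared statistically significant"; no allowance for loss in the calculation; recruitment goal 200.

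**Assumed input.** m is the share per arm whose attendance cannot be observed. The documents give no figure. The range used is 2% to 10%.

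**Step 1: reproduce the plan's figure.** With the unpooled two-proportion formula,

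n = [0.28×0.72 + 0.12×0.88] × (1.960 + 0.842)² / 0.16² = 0.3072 × 7.849 / 0.0256 = 94.2 per group.

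That is 188.4 in total before rounding, so 188 is reproduced. Power at 94 per group, with the pooled variance under the null and the unpooled variance under the alternative, is 78.8%. This is the baseline below.

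**Step 2: unobservable subjects coded as non-attenders, same m in both arms.** The observed rate is p′ = m + (1 − m)p, so the difference becomes (1 − m) × 16 points.

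**Step 3: the same subjects treated as missing.** The rates stay at 28% and 12%, and n becomes 94(1 − m). This assumes that missingness is unrelated to attendance.

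| m | Observed rates if coded as failures | Difference (points) | Power, coded as failures | Power, treated as missing |
|---|---|---|---|---|
| 0% | 28.0% vs 12.0% | 16.0 | 78.8% | 78.8% |
| 2% | 29.4% vs 13.8% | 15.7 | 74.7% | 77.9% |
| 5% | 31.6% vs 16.4% | 15.2 | 68.7% | 76.7% |
| 10% | 35.2% vs 20.8% | 14.4 | 59.6% | 74.4% |

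**Step 4: does the goal of 200 cure it?** 188/200 = 0.94, so 200 recruited leaves 188 evaluable if 6% are missing. With 100 per group and subjects coded as failures, power is 71.4% (m = 5%) or 62.2% (m = 10%). Treated as missing, it is 79.2% or 77.0%. The margin largely offsets missing outcomes in this range. It does not offset the coding.

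**Step 5: unequal loss.** With no true effect (28% in both arms), the spurious difference is (m_control − m_intervention) × 0.72. For 10% vs 5% this is 0.05 × 0.72 = 3.6 points in favour of the intervention; with the shares reversed, 3.6 points against it. With the planned effect, the observed difference would be 35.2% − 16.4% = 18.8 points in the first case and 31.6% − 20.8% = 10.8 points in the second.

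**Step 6: if the 28% already contains movers.** The planning rate is plain clinic non-attendance at the London sites, with reasons not separated. Suppose it includes a share m and the relative effect 12/28 acts only on the remainder. For m = 5%, the intervention rate is 0.05 + 0.23 × 12/28 = 14.9%, and power at 94 per group is 59.4%. For m = 10% it is 0.10 + 0.18 × 12/28 = 17.7%, and power is 38.9%.

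**The case against.** The strongest reply is that the article mostly uses loss to follow-up to mean disengagement from diabetes care. The Background uses it that way, and the 28% drop-out rate is itself defined as clinic non-attendance. On that reading the sentence says only that disengagement is the endpoint and not a reason to inflate the sample. That is right for subjects who remain visible in the database, and database ascertainment with an Ontario-residence criterion should keep the unobservable group small.

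Several further objections stand:

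- A reader might infer that the protocol codes movers, withdrawals and deaths as failures. No passage says so. It follows only from applying the two blanket statements literally.
- A reader might infer that attendance is unknown for everyone lost. It is not: those who stay in Ontario with consent in force remain observed. Death is a known status, not a missing record.
- A reader might infer that the plan has no margin. The calculation has none, but 200 against 188 gives an unlabelled 6%.
- "Factors considered are: future career plans, social situation, and geographic relocation" concerns the choice of age for transition. It shows that relocation is foreseen at this age, not that subjects are expected to leave the province.
- The figure is not visible, so what the footnote's asterisk marks cannot be checked.
- Every loss rate above is assumed. The power figures use the two-proportion comparison behind the sample size, whereas the stated primary test is a mean score test on 0, 1 and 2 sessions.
- Equal misclassification costs power and does not by itself create a false positive.

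Detailed missing-data rules may sit in a full protocol or analysis plan that is not shown, and their absence here is not the point. The point is what the article does state: a reason for making no allowance that is wrong for one group of subjects, and a blanket equation that any later rule would have to contradict.

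**Conclusion.** The concern holds in a limited form. Equating loss to follow-up with the primary outcome is sound for disengagement by subjects still visible in the database. It is unsound for those who leave Ontario or withdraw linkage consent, and for them it does not justify the lack of an allowance.

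The true size cannot be found from the documents. Over an assumed 2% to 10% per arm, coding these subjects as failures costs about 4 to 19 points of power at 94 per group (78.8% to between 74.7% and 59.6%). Treating them as missing costs about 1 to 4 points (77.9% to 74.4%). Most of the loss therefore comes from the coding, not from the smaller number of evaluable subjects. With unequal loss the bias can go either way: a 5-point imbalance gives 3.6 points when there is no true effect. These figures rest on the two-proportion approximation and, except in Step 6, on a 28% rate that excludes unobservable subjects.

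**What to change.** Settle the following before outcome extraction:

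1. Define the event as no adult diabetes specialist visit in the outcome window among subjects still covered by the Ontario database and consenting to linkage.
2. Treat moves out of the province and withdrawn linkage consent as missing outcomes, for example by multiple imputation using arm, the randomization strata and earlier attendance. Keep the coding of all missing outcomes as non-attendance as a sensitivity analysis.
3. Give death its own stated rule, and do not impute attendance for subjects who have died.
4. Replace the sample size sentence with a statement that 188 evaluable subjects are needed and that the goal of 200 allows about 6% unobservable outcomes.
5. Align the Figure 1 footnote with the new definition.

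The cost is wording plus one coverage-status field in the data extraction. No increase over the existing goal of 200 is implied as long as unobservable outcomes stay within about 6%. The downside is that a few outcomes are imputed.

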### Measures

#### **
*Primary outcome*
**

The primary outcome is the proportion of subjects who fail to attend at least one outpatient adult diabetes specialist visit during the second year after transition to adult diabetes care.

#### **
*Secondary outcomes*
**

The secondary objectives of the study are:

1. To compare the frequency of A1C testing in the intervention group (transition program) and the control (standard care) group.

2. To compare the mean A1C levels in the intervention and the control groups.

3. To compare the frequency of testing for microalbuminuria, lipid profile, foot, and retinal examinations between the two groups.

4. To compare the rates of diabetes related emergency room visits and hospitalizations for DKA and hypoglycemia in the two groups.

5. To compare the patient satisfaction and perception of the care during the transition period using self-administered questionnaires.

#### **
*Adverse events and safety*
**

Any occurrence with a serious outcome must be reported to CRO Robarts Clinical Trials within 24 hours of learning about the event. Due to the nature of the intervention, it is not expected that serious adverse events related to the intervention will occur. However, adverse events will be collected from the time of signing the Informed Consent. The following adverse events will be recorded in the subject’s medical records and on the case report form:

• Any medical occurrences requiring medical intervention.

• Any action or outcome (e.g., hospitalization, discontinuation of therapy, etc.) will also be recorded for each adverse event.

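### The primary outcome and sample size are binary (no visit versus at least one), but the declared primary test compares mean scores on 0, 1 and 2 visits, and the stated 80% power was not derived for that test

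*Protocol article*

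**What the plan says.** Under Measures, Primary outcome, the protocol article states: "The primary outcome is the proportion of subjects who fail to attend at least one outpatient adult diabetes specialist visit during the second year". The Abstract has the same definition. This is a yes/no outcome for each patient.

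The section Sample size and statistical analysis begins on the same footing: "The outcome measure used to calculate sample size is the proportion of subjects who fail to attend diabetes clinic visits during the second year". The planning rates are "28% non-attendance rate in the control group compared to 12% in the intervention group", and the result is that "a total of 188 subjects (94 per group) are required to provide 80% power at the 0.05 level of significance".

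The same paragraph then declares a different analysis: "The primary analysis will be based on comparison of subjects in the two treatment groups who attend 0, 1, and 2 sessions" in the follow-up year, and "The Cochran-Mantel-Haenszel mean score test will be used". Covariates are to be handled with a proportional odds model, which is also ordinal. Logistic regression is mentioned later, in general terms and not for the primary outcome. No primary test of the binary proportion is named.

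Table 1 schedules two visits in the follow-up year (months 23 and 28), so 0, 1 and 2 are three distinct levels.

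**The concern.** A mean score test with scores 0, 1 and 2 compares the average number of visits per patient. The stated outcome compares the proportion with none. Two consequences follow.

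First, the planned 16-point fall in non-attendance may come with very different changes in average visits, depending on how attenders divide between one and two. The power of the declared test therefore depends on a quantity that the article does not give.

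Second, the declared test responds to movement from one visit to two. It can reject when non-attendance is the same in both arms. Read against the stated outcome, that result could be reported as lower non-attendance when there was none.

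This is not detail left to an analysis plan. The article states both the outcome and the test, and they disagree. An analysis plan that follows the text inherits the conflict.

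**Working it through.** **Inputs from the article.** Non-attendance 28% (control) and 12% (intervention); 94 per group; two-sided 0.05; 1:1 allocation; visit categories 0, 1, 2.

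**Assumptions.** Scores 0/1/2 (the natural reading, but not stated), one stratum, and the splits between one and two visits shown below.

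**1. The stated sample size reproduces as a binary calculation.** The unpooled two-proportion formula is n = (1.96 + 0.84)² × [p₁(1−p₁) + p₂(1−p₂)] / (p₁−p₂)². With 0.28 × 0.72 = 0.2016 and 0.12 × 0.88 = 0.1056, n = 7.849 × 0.3072 / 0.0256 = 94.2 per group, which matches 94. At 94 per group, power is 78.8% by the pooled formula and about 80% by simulation. The size is sound for the binary test. (The "A 60% relative reduction in non-attendance rate is considered clinically important" sentence is a rounding: 28% to 12% is 16/28 = 57%.)

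**2. Why the declared test behaves differently.** Suppose 36% make two visits in both arms and the whole effect is from no visit to one: 28/36/36 versus 12/52/36.
- Mean visits: 0.36 + 2 × 0.36 = 1.08 versus 0.52 + 2 × 0.36 = 1.24, a difference of 0.16.
- Averaging the arms gives 20/44/36, with mean 1.16 and variance 0.44 + 4 × 0.36 − 1.16² = 0.534, so SD 0.731.
- Standard error: 0.731 × √(2/94) = 0.107. Ratio: 0.16/0.107 = 1.50. Approximate power: Φ(1.50 − 1.96) = 32%.
- On the binary scale the difference is also 0.16, but the SD is √(0.20 × 0.80) = 0.40. The ratio is 0.16/0.0583 = 2.74.

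The difference is the same. The spread between one and two visits adds noise.

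**3. Proportional odds case.** The odds ratio is (0.88/0.12)/(0.72/0.28) = 2.85. With 36% of controls at two visits, the intervention proportion has odds 0.5625 × 2.85 = 1.60, that is 61.6%.

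**4. Simulated rejection rates** (200,000 trials per row, 94 per group, percentages with 0/1/2 visits):

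| Assumed pattern | Control | Intervention | Mean score | Binary |
|---|---|---|---|---|
| Only 0 to 1 | 28/20/52 | 12/36/52 | 28% | 80% |
| Only 0 to 1 | 28/36/36 | 12/52/36 | 32% | 80% |
| Only 0 to 1 | 28/50/22 | 12/66/22 | 40% | 80% |
| Same two-visit share of attenders | 28/36/36 | 12/44/44 | 60% | 80% |
| Same two-visit share of attenders | 28/20/52 | 12/24/64 | 67% | 80% |
| Proportional odds | 28/36/36 | 12/26/62 | 96% | 80% |
| Proportional odds | 28/12/60 | 12/7/81 | 89% | 80% |
| Equal non-attendance, 20 points from 1 to 2 | 28/36/36 | 28/16/56 | 37% | 5% |
| Equal non-attendance, 20 points from 1 to 2 | 20/50/30 | 20/30/50 | 45% | 5% |

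Under the same-share pattern, power rises toward 80% as attenders become nearly all one-visit or nearly all two-visit. Under proportional odds it falls to 82% when almost all attending controls make both visits (28/2/70).

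**The case against.** The strongest defence is that the ordinal test suits the trial's aim. The Aim of the study is better clinic attendance, and the primary objective speaks of regular care, so a test that also credits a second visit is reasonable. If the program raises attendance at every level, as under proportional odds, the test has more power than the binary one. The 37-45% rejection rates are not false positives for the hypothesis that the test addresses. They detect an assumed real 20-point gain in two-visit attendance. All this stands. What remains is that the article names a different primary outcome and powers the trial on it, so such a gain could be misread as lower non-attendance.

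A reader might infer several stronger claims that the documents do not support:
- *The trial is underpowered.* Power of the declared test may lie below or above 80%. The lowest figures need every regained patient to attend exactly once.
- *The test gives less weight to the step from no visit to one.* With scores 0/1/2 both steps count equally. The loss comes from variance among attenders.
- *The scale has no room for a third visit because adult visits occur three times a year.* That spacing (months 10, 14, 18) belongs to the intervention phase. The outcome year schedules two, and coding of any extra visit can be left to the full plan.
- *The scores might be 0/1/1, which would remove the problem.* That would reproduce the binary test, but separating one visit from two and adding a proportional odds model would then serve no purpose.

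**Conclusion.** The point holds as a mismatch between the stated primary outcome and the declared primary test. The 188 patients are right for the binary comparison, and the arithmetic is not at fault. The 80% simply was not calculated for the mean score test, whose power cannot be derived from the article. Under the assumed splits it runs from about 28% to about 97%. The case that is neutral about second visits gives 60-67% for mid-range splits.

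These figures rest on scores 0/1/2, an unstratified test and splits that the article does not supply. The mismatch itself rests on none of these. Since it affects the trial's main conclusion and can be settled in wording, it should be corrected before analysis.

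**What to change.** Make the primary test the Cochran-Mantel-Haenszel 2x2 comparison of zero versus at least one adult specialist visit in the outcome year, stratified by the randomization factors (centre and visit 1 A1C). Report the risk difference with a 95% confidence interval, and use logistic regression for covariate adjustment. Move the mean score test and the proportional odds model to secondary analyses.

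This needs no new data or patients, and the stated sample size then holds at about 80% power. The cost is the ordinal test's extra power if the effect follows proportional odds: up to about 17 points (97% against 80%).

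If the sponsor prefers the ordinal test, the primary outcome must be redefined as ordered attendance wherever it appears. The scores must be stated, and power restated for an assumed 0/1/2 distribution in each arm.
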